#### Planned statistical methods

Statistical Considerations Baseline is defined as the randomization visit and the end of the trial is defined as the final visit. Categorical data will be summarized by treatment group, using the number and percentages of subjects.For the calculation of percentages, the denominator will be the number of subjects in the analysis set.Continuous data will be presented using the number of subjects, mean, standard deviation, median, lower quartile, upper quartile, minimum, and maximum. Both the absolute values and the change from baseline will be presented. The treatment group and visit will present descriptive statistics for all endpoints (if applicable). All statistical tests will be carried out as two-sided and performed on a 5 % significance level. Estimated treatment differences and 95% CIs will be presented together with the corresponding *p*-value. All safety endpoints will be presented using descriptive statistics and no formal statistical tests will be applied.The evaluation of continuous variables of the characteristics between the groups will be analyzed by the *t*-test or Mann-Whitney.The assessment of variation of serum levels of biomarkers, muscle mass, and strength between groups and time will be done by the mixed regression models.Kaplan-Meier survival curves will be used to show the survival in the groups within 90 days. Considering day zero as the day of randomization and entering into the study, patients related the final date they had each outcome. This is appropriate as it takes into account what happened during the course of the study. *P*-values were obtained through proportional Cox regression models and a value of 5% was considered statistically significant.All adverse events will be summarized. The summaries will include the number of events, the number of subjects, and the proportion of subjects reporting these events and will be tabulated by system organ class.

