### Outcomes

The primary outcomes will be functional capacity, strength, and changes in muscle mass after the intervention. The evaluations will be conducted in the first 24 hours after stroke and on the 7^th^ day of hospitalization. The patients will be assessed for the following:Functional capacity according to the mRs and Timed Up and Go test scores.Muscle strength according to handgrip strength and lower limb strength according to the National Institutes of Health Stroke Scale (NIHSS) score.Muscle mass by muscle ultrasonography, electrical bioimpedance, and muscle degeneration markers by D3-methylhistidine.

A descriptive and comparative evaluation between groups in order to verify the inflammatory and potential serum biomarkers behavior during hospitalization will be performed with all participants randomized.

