### Procedures (template)

All patients with ischemic stroke confirmed by imaging examinations who meet the study inclusion criteria will be invited to participate. After signing the informed consent form, the patients will be randomized to the intervention or control groups. All patients will undergo clinical and neurological evaluations conducted by the medical team using the NIHSS score, which is used to determine treatment and predict prognosis; Bamford classification according to brain injury location; and the Alberta Stroke Program Early CT Score (ASPECTS), which verifies the extent of the injury [1, 21].

The template for the recommended schedule of enrollment, interventions, and assessments is presented in Fig. 2. To verify the occurrence of mortality, we will utilize death certificates from medical records.

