### Randomization and blinding

For all subjects, the screening visit and the enrollment visit were performed on the same day. Subjects were randomized 1:1 to the intervention or control groups. The randomization was performed using a cell phone application, which creates a random control and intervention sequence, and was performed in 10 out of 10 participants. No stratification factor was used.

To maintain the blindness of the study, randomization will be performed by a person uninvolved in data collection and data analysis. The participant, the professional responsible for administering the supplements, and the person responsible for conducting the protocol assessments will be blinded to the intervention. The professional in charge of the statistical analysis of the data will not be blinded to the intervention.

Breaking the blinding will be allowed if the participant has a serious adverse effect related to the supplementation, such as an allergic reaction. In this case, the principal investigator will be responsible for breaking the blinding and for informing the hospital’s medical staff about which supplement the participant was consuming.

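### The primary domain functional capacity (mRS, Timed Up and Go) has no assigned analysis, and no comparison uses admission NIHSS in an unstratified trial of 30 patients

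*Protocol article*

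**What the plan says.** All references are to the protocol article.

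- **Outcomes.** "The primary outcomes will be functional capacity, strength, and changes in muscle mass after the intervention". The first domain is defined as "Functional capacity according to the mRs and Timed Up and Go test scores". Assessments are in the first 24 hours and on day 7, so every primary measure has a scheduled baseline.
- **Planned statistical methods.** Mixed models are assigned by outcome: "variation of serum levels of biomarkers, muscle mass, and strength between groups and time will be done by the mixed regression models". Survival gets Kaplan-Meier curves and Cox regression, and safety is descriptive. The remaining test is introduced by "The evaluation of continuous variables of the characteristics between the groups will be analyzed by the" t-test or Mann-Whitney. For reporting, "Both the absolute values and the change from baseline will be presented". No covariate is named for any comparison.
- **Procedures.** "All patients will undergo clinical and neurological evaluations conducted by the medical team using the NIHSS score", and the same sentence recognises that this score predicts prognosis.
- **Randomization and blinding.** Allocation is 1:1 and "No stratification factor was used". The statistician is not blinded to allocation.
- **Sample size.** 15 per group.

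**The concern.** The methods section goes through the outcomes and gives each a method. It reaches the exploratory biomarkers but leaves out the first-named primary domain. An analyst who knows the allocation would have to choose the analysis of mRS and Timed Up and Go. The section also promises treatment differences with 95% confidence intervals, but for mRS, a 0 to 6 scale on which death scores 6, it does not say what the difference would be.

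The second limb is precision and balance. Stroke severity is likely to bear on function and strength at day 7. With small arms and no stratification, a chance difference in severity can shift an estimate noticeably. The measurement that would correct for it is already taken on everyone, and the stated analyses do not use it.

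**Working it through.** **1. The plan's own figure.** The cited meta-analysis averages 10 patients per arm; 50% more gives 10 × 1.5 = 15 per group, which reproduces. The article gives no effect size, SD, correlation or power, so those below are assumptions.

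**2. Outcomes against methods.**

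| Primary domain (Outcomes) | Method (Planned statistical methods) |
|---|---|
| Functional capacity: mRS, Timed Up and Go | none named |
| Strength: handgrip, NIHSS leg item (scored 0 to 4) | mixed regression |
| Muscle mass: ultrasound, bioimpedance, D3-methylhistidine | mixed regression |

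If the t-test/Mann-Whitney sentence means patient characteristics, functional capacity has no test. If it is stretched to cover functional capacity, the test is unadjusted, and mRS is not a continuous variable.

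**3. Chance imbalance.** The SD of a between-arm difference in a standardised baseline factor is √(1/15 + 1/15) = √(2/15) = 0.365. P(|difference| > 0.5 SD) = 2 × [1 − Φ(0.5/0.365)] = 0.171, or 17%. For more than 0.25 SD it is 49%, and for more than 0.75 SD it is 4%.

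**4. Precision for continuous outcomes.** Let ρ be the correlation between baseline and day 7, with equal variances. Relative to the day-7 variance:

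- day 7 only: 1
- change score: 2(1 − ρ)
- baseline-adjusted: 1 − ρ²

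With two visits and free baseline means, the group-by-time term is the change-score difference. In a simulated set of 15 against 15, both estimates were 0.227. Adjusted over change-score variance is (1 − ρ²)/[2(1 − ρ)] = (1 + ρ)/2.

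| ρ (assumed) | Change score | Adjusted | Saving vs change score | Saving vs day 7 only |
|---|---|---|---|---|
| 0.5 | 1.00 | 0.75 | 25% | 25% |
| 0.7 | 0.60 | 0.51 | 15% | 49% |
| 0.8 | 0.40 | 0.36 | 10% | 64% |

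These formulas ignore the cost of estimating the slope. For one normally distributed baseline covariate and 30 patients, that cost is an expected factor of 1 + 1/(30 − 4) = 1.038, so the adjusted variances are in practice about 4% higher.

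**5. Illustrative power.** Assume a 0.8 SD effect on a continuous measure, 15 per arm, two-sided 5%, noncentral t:

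| ρ (assumed) | Day 7 only | Change score | Adjusted |
|---|---|---|---|
| 0.5 | 56% | 56% | 68% |
| 0.7 | 56% | 78% | 84% |

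**6. Conditional bias when the outcome's baseline differs by 0.5 SD.** Day 7 only: 0.5ρ, which is 0.25 to 0.40 SD for ρ from 0.5 to 0.8. Change score: 0.5(ρ − 1), which is −0.25 to −0.10 SD. Baseline-adjusted: 0.

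**The case against.** The strongest reply is that covariates, degrees-of-freedom methods and baseline constraints usually belong in an analysis plan, which is not shown, and that an article condenses further. That is fair for covariates, so this limb is an inexpensive improvement and not an error. It does not cover functional capacity, because the article itself lists which outcomes are modelled and leaves out a primary one.

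Four stronger readings are tempting, and the document does not support them:

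- **That no comparison accounts for baseline.** The mixed models run over group and time, and the first visit is the baseline, so baseline is in them. The article does not say whether baseline means are free or constrained. If they are constrained equal, the loss in step 4 essentially disappears.
- **That mRS and Timed Up and Go have been assigned an unadjusted test.** That sentence most naturally concerns patient characteristics. The accurate statement is that no method is named.
- **That a linear model is imposed on the ordinal NIHSS leg item.** The article says mixed regression, which can include ordinal forms. The form is unstated.
- **That the unadjusted tests are invalid.** Chance imbalance is already allowed for in a valid 5% test. What is lost is precision and protection against bias conditional on the imbalance that occurs.

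The gap between 56% and 68% or 84% power also does not describe the modelled outcomes. There, at ρ = 0.7, the comparison is 78% with 84%. Nor does it describe mRS, for which an ordinal model is proposed and no power was computed.

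**Conclusion.** The point holds in two parts of unequal weight. The main one can be read directly from the text: functional capacity is primary and has no assigned analysis. The secondary one is that admission NIHSS is unused in an unstratified trial with 15 per arm, where the chance of a difference above 0.5 SD in a given factor is 17%. The outcome's own baseline in a mixed model does not replace a severity covariate.

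For biomarkers, muscle mass and strength, the gain from baseline adjustment is modest: about 25% less variance at ρ = 0.5 and 15% at ρ = 0.7, before the small slope cost, and only if baseline means are left free. These figures assume ρ, equal variances and complete data. The power figures also assume a 0.8 SD effect, and all of them are illustrative.

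**What to change.** State in the plan, outcome by outcome:

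- **Continuous muscle mass, strength and biomarker measures:** adjust for the baseline value (or constrain baseline means equal across arms) and for admission NIHSS, with small-sample degrees of freedom.
- **mRS (death = 6) and the 0 to 4 NIHSS leg item:** ordinal regression adjusted for admission NIHSS, with the odds ratio and its 95% confidence interval as the treatment difference.
- **Timed Up and Go:** a rank-based or ordinal model adjusted for admission NIHSS.
- **D3-methylhistidine:** only 10 of the 30 patients are analysed, leaving 10 − 2 = 8 residual degrees of freedom before any covariate. Use at most the baseline value.

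Because the analyst is not blinded and recruitment began in March 2019, date and document these choices before any unblinded look at the data.

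The cost is wording, plus one or two of the 30 − 2 = 28 degrees of freedom in the full sample. No new data are needed. Covariates should stay at one or two with this sample size.

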### Follow-up evaluations

A follow-up 90 days after stroke will be conducted to verify functional capacity, muscle strength, mortality, and quality of life. The following will be assessed in each patient:Functional capacity according to the mRs and Timed Up and Go test scores.Muscle strength based on handgrip strength and lower limb strength according to NIHSS score and the 30-s chair stand test score.Patient perception of quality of life according to The European Quality of life Scale Five Dimension (EuroQol-5D) score.

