### Sample size

We reviewed a study that analyzed the effects of creatine supplementation in 18 healthy older people, in which 10 patients were allocated to the creatine group and 8 to the control group. The authors observed an improvement in muscle strength, weight, and fat-free mass in the group that received supplementation [22]. In addition, a meta-analysis based on this previous study included approximately 600 patients from 60 studies, with an average of 10 patients in each arm per study [16]. Considering that this is a study on creatine supplementation in patients after stroke, we decided to include 50% more in the convenience sample, with a total of 15 patients in each group.

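### The 90-day survival p-value is fixed as a Cox p-value with 15 patients per arm and no fallback, though too few deaths for a usable Cox result is a real possibility

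*Protocol article*

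**What the plan says.** The protocol article, under Planned statistical methods, sets out the survival analysis: "Kaplan-Meier survival curves will be used to show the survival in the groups within 90 days". The test follows: p-"values were obtained through proportional Cox regression models", with 5% as the threshold for significance. Two general rules in the same section apply: "All statistical tests will be carried out as two-sided and performed on a 5 % significance level", and "Estimated treatment differences and 95% CIs will be presented together with the corresponding" p-value.

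Under Follow-up evaluations, mortality is one of the things the 90-day visit is meant "to verify functional capacity, muscle strength, mortality, and quality of life". It is not among the primary outcomes listed under Outcomes.

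Under Sample size, the number is a convenience choice: "we decided to include 50% more in the convenience sample, with a total of 15 patients in each group". No event rate, expected number of deaths or power is given there or elsewhere.

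The article does not say whether the Cox p-value is a Wald, score or likelihood-ratio p-value. It names no alternative for the case of few deaths or none in an arm.

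**The concern.** A Cox hazard ratio exists only if the partial likelihood has a maximum. When all deaths fall in one arm it has none. The likelihood keeps rising as the log hazard ratio moves away from zero, and the standard error grows without bound. The estimate and confidence interval that the plan promises then cannot be produced in the usual way, and the Wald p-value says nothing about the data. With 30 patients this situation can arise by chance alone.

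If the analyst turns to another p-value from the same model, the result depends on which one is taken. The large-sample approximations behind these p-values are poor with a handful of deaths. The trial could report a survival difference at the 5% level that an exact test would not support, or report no usable result. The article's Discussion says the trial should inform larger studies, so a misleading survival p-value could be carried forward.

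**Working it through.** **Inputs.** 15 patients per arm (Sample size; 10 per arm plus 50% is 10 × 1.5 = 15, which reproduces the stated figure). Two-sided 5% level and 90-day horizon (Planned statistical methods). The 90-day death risk p is not in the document, so it is an assumption and a range is shown. Follow-up is taken as complete to day 90.

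**Step 1: chance of an arm without deaths.** One given arm has none with probability (1−p)^15. At least one of the two has none with probability 1 − (1 − (1−p)^15)².

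| Assumed mortality, both arms | Expected deaths of 30 | One given arm has none | At least one arm has none |
|---|---|---|---|
| 5% | 1.5 | 0.463 | 0.71 |
| 10% | 3.0 | 0.206 | 0.37 |
| 15% | 4.5 | 0.087 | 0.17 |
| 20% | 6.0 | 0.035 | 0.07 |

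The last column passes one half only when mortality is below about 7.9%. With unequal risks of 10% v 5% it is 0.57, and with 20% v 10% it is 0.23. The chance of no deaths in either arm, where no Cox model can be fitted at all, is 0.463² = 0.21 at 5% and 0.206² = 0.04 at 10%.

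**Step 2: what Cox gives when one arm has none.** With 3 v 0 deaths, the partial likelihood evaluated at log hazard ratios of −5, −10 and −20 gives standard errors of 6.8, 83 and 12,265. The corresponding Wald p-values are 0.46, 0.90 and 0.999. With 5 v 0 the Wald p also drifts to 0.998, although Fisher's exact p is 0.042. The Wald p therefore tends to 1 whatever the split.

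**Step 3: the finite alternatives from the same model.** With all deaths in one arm and complete follow-up, these depend only on the risk sets. For 3 v 0:

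- Likelihood ratio: 2 × [(ln 30 + ln 29 + ln 28) − (ln 15 + ln 14 + ln 13)] = 2 × (10.101 − 7.912) = 4.38, p = 0.036.
- Score (log-rank): U = 15/30 + 15/29 + 15/28 = 1.553, information = 0.748, U²/information = 3.22, p = 0.073.
- Fisher: 2 × C(15,3)/C(30,3) = 2 × 455/4060 = 0.224.

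| Deaths | Likelihood ratio p | Score p | Fisher p |
|---|---|---|---|
| 3 v 0 | 0.036 | 0.073 | 0.224 |
| 4 v 0 | 0.014 | 0.035 | 0.100 |
| 5 v 0 | 0.0055 | 0.016 | 0.042 |

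**Step 4: error rate under no treatment effect.** Every ordering of deaths between two arms of 15 was enumerated, given the total number of deaths. The share with p < 0.05 is:

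| Total deaths | Likelihood ratio | Score | Fisher |
|---|---|---|---|
| 3 | 22.4% | 0% | 0% |
| 4 | 10.0% | 10.0% | 0% |
| 5 | 4.2% | 4.2% | 4.2% |
| 6 | 1.7% | 1.7% | 1.7% |
| 7 | 8.0% | 8.0% | 0.6% |
| 8 | 3.5% | 3.5% | 3.5% |

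The excess is not uniform, but it falls on plausible totals: 3 deaths is the expected number at 10% mortality. The exact test stays at or below 5% throughout.

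**The case against.** **The article never says Wald.** This stands. A reader might infer that the plan will report a p-value near 1 for a strong split, but the text says only that p-values come from Cox regression. Score and likelihood-ratio p-values stay finite. They do not rescue the rule, however: Step 4 shows that both can exceed the nominal 5%, and Step 3 shows that they can fall on opposite sides of it for the same data.

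**A Wald p near 1 beside a significant exact test is rare.** This also stands. Fisher's test reaches 5% only from 5 v 0 upwards. The chance that one arm has no deaths and the other at least five is 2 × (1−p)^15 × P(at least 5 of 15). At equal mortality of 5, 10, 15 or 20% that is 0.06, 0.5, 1.1 or 1.2%. At 20% v 10% it is 3.4%. The more common trouble is the lack of an estimate and interval, or a p-value that is too small.

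**Nothing would be rescued.** For a hazard ratio of 0.5, 80% power needs about 66 deaths (Schoenfeld formula), and with 3 to 6 deaths the power is about 9 to 13%. An exact test does not change that. It is proposed for validity, not for power. The Kaplan-Meier curves would also let readers see a lopsided split.

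**Sparse-event detail belongs in the statistical analysis plan.** That is fair for a fallback alone. But the article itself fixes the method, and the method is poorly suited to the sample size that it also fixes.

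**Conclusion.** The concern holds as a limited point about a follow-up outcome. The survival p-value is tied to Cox regression in two arms of 15 with no fallback. An arm without deaths has a probability of 71, 37, 17 or 7% at an assumed 5, 10, 15 or 20% mortality, and Cox then yields no finite hazard ratio and no usable Wald interval or p-value. The unnamed choice of statistic leaves the conclusion open. Under no effect, the likelihood-ratio test rejects 22% of the time with 3 total deaths. Both it and the score test reject 10% of the time with 4 and 8% with 7.

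A reader might go further and call an arm without deaths likely. The document does not support that, because it gives no mortality rate and the chance exceeds one half only below about 8%. The exclusion of hemodynamically unstable and ventilated patients points towards a lower rate but supplies no figure. The results assume complete 90-day follow-up and, in the main table, equal risk in both arms. The primary outcomes are not affected. The change is worth making because it is cheap and must be settled before the data are seen.

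**What to change.** Keep the Kaplan-Meier curves. Replace the Cox p-value with one from an exact (permutation) log-rank test, two-sided at 5%. Report the number of deaths per arm and the 90-day risk difference with an exact or score-type 95% CI as the main effect measure. If a hazard ratio is wanted, give it only as a supplement, from Firth-penalised Cox regression with a profile-likelihood interval.

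This takes a sentence or two in the analysis plan and changes no data collection. The cost is that the exact test is conservative: in the tables above, 3 or 4 deaths in total cannot reach 5% however they split. The main survival measure also becomes a risk difference instead of a hazard ratio.

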#### Sensitivity analysis

The primary analysis will be repeated using the PP and safety analysis set. We will perform analysis using only patients with specific symptoms to each symptoms.

### Data monitoring

The study follows the schedule of the Research Ethics Committee of Sao Paulo State University with the submission of partial reports to assess the progress and conduct of the study. At the end of the study, the final report will be sent with all the results. As this is an intervention with a low risk of serious adverse events, with a supplement known to be safe at the doses administered in the study, interim analyzes are not foreseen before the end of the study.

Non-serious adverse events such as diarrhea, dyspepsia, and abdominal pain related to supplementation will be analyzed individually and discussed with the assisting medical team to assess what action will be taken. Serious adverse events related or not to the intervention, such as death, acute kidney injury, infection with prolonged hospitalization, and hospitalization for any cause will be reported to the institution’s Research Ethics Committee within 24 h of their occurrence. All adverse events will be summarized. The summaries will include the number of events, the number of subjects, and the proportion of subjects reporting these events.

Monthly team meetings are held with the principal investigator to align the protocol, verify the progress of the study, and ensure compliance with deadlines. Additionally, the study will have an external endpoint adjudication committee composed of three physicians independent from investigators and the sponsor to investigate adverse events.

